Recent literature suggests that AS of small, low risk PTC (confined to the thyroid), is safe (7). In a recent systematic review and meta-analysis of long-term outcomes of patients with small, low risk PTC under AS, Cho et al. reported that only 5.3% of patients experienced tumor growth ≥3 mm in maximal diameter and 1.6% of patients developed nodal metastases during 5 years of follow-up (7). No thyroid cancer-related deaths nor incident distant metastases have been observed in patients with small, low risk PTC under AS (8). However, most of the published literature on AS includes primarily patients with papillary microcarcinoma (PTC 1cm or smaller in largest diameter) (7), which may not routinely necessitate biopsy, per recent ATA clinical practice guidelines guidance (5). In 2016, in Toronto, we initiated a multi-phase prospective observational study of patients with small, low risk PTC < 2cm in maximal diameter (i.e. including PTC larger than microcarcinoma), which we refer to as very low risk PTC (VL-PTC) (9). In the Toronto study, we offer patients a choice of surgery or AS and report their disease management decision (decision-making phase of the study) (9). We also prospectively report patient outcomes in patients choosing AS or surgery (Clinicaltrials.gov: NCT03271892) (9). An interim analysis on the disease management decisions of the first 100 patients enrolled in the Toronto study was recently published (10). About half of the enrolled patients in the Toronto study have a PTC larger than a microcarcinoma (10). We reported that 71.0% (71/100) of our patients chose AS over surgery and patients’ rationale for the decision was described in detail using a qualitative approach (10). Although the high percentage selecting AS may in part reflect some referral bias (both self-referral of patients who are interested in AS and referral from thyroid cancer specialists whose patients specifically request AS), these preliminary data suggest that among Canadians with VL-PTC there is substantial interest in being offered the choice of AS as an alternative to surgery (10). One of the main reasons why our patients chose AS, was a desire to avoid immediate thyroid surgery, with the potential implications of thyroid hormone treatment (10). In contrast, patients who chose surgery wanted to remove any thyroid cancer in their body (i.e. aspired for cure of the disease). Recruitment in the Toronto prospective, observational AS decision-making study is now complete (200 patients), (with a full report on disease management decisions forthcoming). Furthermore, long-term patient follow-up is ongoing in the Toronto study. In response to a) popularity of the option of AS in patients with small, low risk PTC in the Toronto study (10), b) recently acquired knowledge in this area (in the published literature and clinical practice guidelines), and c) recent interest among Canadian thyroid cancer specialists, we have developed a prospective observational pan-Canadian study examining long-term clinical and patient-reported outcomes on AS and surgery for VL-PTC. The proposed study, described below, is similar to design to the original Toronto study, but with a focus on clinical outcomes and patient reported outcomes over a long period of follow-up.

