### The Study Population Eligibility Criteria and Recruitment

Consenting adults (age ≥18 years) with surgically untreated PTC < 2cm in maximal diameter that is confined to the thyroid, not encroaching on critical structures in the neck (e.g. trachea or recurrent laryngeal nerve), with no evidence of extrathyroidal extension nor nodal metastases (which we refer to as very low risk PTC, VL-PTC), are eligible for inclusion in the study (**Table 1**). Several minor changes in the original Toronto inclusion and exclusion criteria are also detailed in **Table 1**, largely enabling recruitment of interested patient groups (such as those with other low risk malignancies or other thyroid or parathyroid disease for which there is no absolute indication for surgery– see **Table 1**). Data from patients who consented to long-term follow-up in the original Toronto study (NCT03271892) will be reported with data from the additional patients recruited in the multi-centre study (NCT04624477).

**Table 1 T1:** Eligibility criteria.

Participant Inclusion and Exclusion Criteria	
*Inclusion criteria*	*Exclusion criteria*
•Age 18 years or older	•Thyroid cancer that is known to have extended beyond the thyroid (e.g. extrathyroidal extension, nodal or distant metastases)
•Newly diagnosed, untreated papillary thyroid cancer (PTC) < 2cm in maximal diameter on ultrasound imaging. The fine needle aspiration biopsy cytology of the primary tumor is required to be read as PTC or suspicious for PTC*	•A history of prior thyroid surgery*
•Absence of metastatic cervical lymphadenopathy on imaging (ultrasound the neck or other)	•The primary PTC is encroaching the recurrent laryngeal nerve or trachea (which is considered at potential high risk for invading these structures in the event of disease progression)
•No other absolute* indication for thyroid or parathyroid surgery at the time of the assessment	•Proven or suspected poorly differentiated or non-papillary thyroid cancer
•Patient must grant permission for review of thyroid cancer-related medical records	Medically unfit for surgery due to severe co-morbidity. Severe comorbidity may include another active malignancy with limited life expectancy of < 1 year*
	•Pregnancy at the time of study enrollment
	•One or more absolute indications for thyroid or parathyroid surgery (other than thyroid cancer)*

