Patient recruitment at all study sites is focused in participating thyroid cancer clinics, although eligible patients may be referred by healthcare providers or refer themselves by contacting a study centre. Screening for eligibility in consenting patients is performed by a research assistant, under the supervision of a site investigator. All patients are required to have at least one consultation by a thyroid cancer surgeon (at any institution) such that the type of surgery that would be recommended for the particular case, as well as potential complications, are explained in detail (as per usual clinical practice of the surgeon). Participants are informed about the options of AS and surgery and provided written handout summarizing the relevant literature on both AS and surgical options, and given the opportunity to meet with a study physician to discuss the provided information and obtain answers to any related questions. Patients are free to make their own disease management choice and the clinical disease management course (i.e. surgery or AS) is not assigned by the investigators in the study. Baseline neck imaging studies are reviewed by a study investigator experienced in interpretation of neck ultrasound or a radiologist with expertise in ultrasound who is familiar with the study, to confirm eligibility. Training on evaluation of ultrasounds for baseline assessment and follow-up has been provided at a national investigator meeting ([name], [name]) and will be revisited during the course of the study at yearly (or more frequent) investigator meetings. The central study co-primary investigators ([name], [name]) are available to advise and support the other investigators throughout the study. A REDCap database has been developed by the THETA Group at University Health Network, for centralized electronic collection of data entered by research staff at each study site.

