
**Table 2 T2:** Definition of disease progression.

Definition of progression of papillary thyroid cancer under active surveillance for which salvage surgery is advised (one or more of the criteria listed below)*
1. Primary index PTC growth >3 mm (in the largest dimension), confirmed on two consecutive ultrasound exams. The 3 mm size cut off is considered reproducible (21)
2. Primary PTC growth in a location that is concerning (e.g. immediately adjacent to the trachea or in the course of the recurrent laryngeal nerve) (22)
3. Incident development of metastatic PTC to lymph nodes (confirmed on cytology or unequivocal imaging)
4. Incident development of distant metastatic PTC (confirmed on imaging or biopsy or surgical histology)

*Patients may choose to have surgery in absence of disease progression at any time point in follow-up.

Thyroid cancer-related medical records will be reviewed by study staff at least yearly, for up to 10 years, regarding thyroid cancer outcomes, treatments, and potential treatment-related complications. Patient questionnaires/interviews and communication scripts are in English for most study sites, but in (Quebec/Canadian) French for Quebec sites.

For patients recruited in the multi-centre study, a baseline self-administered written questionnaire includes demographics and medical history, a question on baseline disease management preference, as well as the following patient-reported outcomes: i) quality of life (thyroid cancer/cancer-specific - EORTC QLQ-THY34 (12) with EORTC QLQ-C30 (13) and ii) anxiety (Generalized Anxiety Disorder Screener, GAD-7) (14). Patients recruited from the original Toronto study who had previously completed a baseline questionnaire as outlined in the original study protocol (10), will not perform a repeat baseline assessment, but relevant original baseline data will be reported.

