### Statistical Analysis

Descriptive data will be presented in the surgical and AS groups for baseline demographic characteristics, medical history, initial disease management choice (surgery or AS), patients’ rationale for their choice, thyroid cancer treatments, and thyroid hormone treatment. Summaries of follow-up date will tabulate major complications of thyroid cancer surgery (i.e. clinically diagnosed hypoparathyroidism or recurrent laryngeal nerve injury beyond the first year after any thyroid cancer surgery), most recent PTC disease status, proportions crossing over from AS to surgery (and indication), and deaths (thyroid cancer-specific and overall, respectively).

The primary analysis will separately estimate the cumulative incidence of ‘failure’ of disease management (along with 95% confidence intervals) at any given time since enrolment in the AS and surgical arms, using the Kaplan-Meier method. The differences in cumulative incidence will also be calculated (with 95% confidence intervals).

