For categorial outcomes, we will report proportions with 95% confidence intervals according to AS or surgical group. For all categorical clinical outcomes for which there is a sufficient number of events for meaningful analysis, we will compare the AS and surgical groups using competing risks models. We will summarize the following secondary patient-reported outcomes in each group: i) quality of life (thyroid cancer/cancer-specific) (12, 13), ii) anxiety (14), iii) survivor concerns (16), and iv) decision regret (15) (relating to the original decision on VL-PTC disease management). The data will be reported at last available study follow-up, with data from prior time points analyzed in interim analyses, if there are sufficient patients and events for meaningful analysis. All questionnaire data will be scored as per developers, for total scores or subscale scores. Where patient reported outcomes are missing and patients are known to be alive, multiple imputation will be used, with other outcomes one the same patient at the same time or other times in the imputation model. For each questionnaire outcome, we will calculate summary statistics to characterize the cohort at the last follow-up. Analyses will be adjusted for baseline variables, including age, sex, and primary tumor size (≤ 1cm or > 1cm) as well as duration of follow-up. If sufficient data are available for meaningful analysis will examine predictors of psychosocial health outcomes (e.g. age, sex, primary tumor size) if sufficient data are available for meaningful analysis. Clinical outcomes will also be compared between men and women, if there are sufficient events.

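### The adjusted secondary and patient-reported comparisons enter tumour size only as a split at 1 cm, although diameter is measured; a continuous term would leave less residual confounding if size matters within the bands

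*Protocol article*

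**What the plan says.** The Statistical Analysis section states: "Analyses will be adjusted for baseline variables, including age, sex, and primary tumor size (≤ 1cm or > 1cm) as well as duration of follow-up". The size term is thus fixed at two levels: "primary tumor size (≤ 1cm or > 1cm". The sentence stands in the paragraph on categorical secondary outcomes and questionnaire outcomes, after the description of how each questionnaire will be summarised.

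A finer measurement exists. Table 1 (Eligibility criteria) requires "Newly diagnosed, untreated papillary thyroid cancer (PTC) < 2cm in maximal diameter on ultrasound imaging". Table 2 (Definition of disease progression) uses growth of more than 3 mm in the largest dimension as a criterion and treats 3 mm as a reproducible difference.

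The groups are self-selected. The recruitment section says that "the clinical disease management course (i.e. surgery or AS) is not assigned by the investigators in the study". The Sample Size Calculation section says that the surgical arm is recruited so that secondary outcomes can be compared with control. The Introduction reports that about half of the Toronto patients have a tumour above the 1 cm microcarcinoma limit.

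**The concern.** Without randomisation, the secondary comparisons of AS and surgery are only as good as the adjustment. Size is one of the few covariates named, and the plan fixes its form: a tumour of 1.1 cm and one of 1.9 cm get the same value. Within the 1-2 cm band, about half of the Toronto patients, the model makes no size adjustment at all. The same holds within the band at or below 1 cm.

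If larger tumours within a band lead more patients to choose surgery, and also go with worse (or better) scores, part of that difference will be read as an effect of management. The data to reduce this are already collected.

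**Working it through.** **The plan's own figures.** The document gives no figure for this adjustment. Its 328 AS patients come from the precision of a single proportion. With an exact (Clopper-Pearson) interval around 3%, the expected half-width at n = 328 is 0.0199, which agrees with the stated 2%. The surgical number follows as 328/3 = 109.3, about 110. No size covariate enters these figures, so they stay as they are.

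**What a split leaves.** Suppose that the outcome is linear in size, with slope β per cm, and that management has no true effect. The crude AS-surgery difference is then β times the difference in mean size between the arms. After adjustment for the 1 cm indicator, what remains is β times the pooled *within-band* difference in mean size. The share left is the within-band difference divided by the crude difference.

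**Inputs.**
- From the document: diameter below 2 cm, cut at 1 cm, AS:surgery ratio 3:1 (25% surgery), expected arms of 330 and 120, about half of Toronto tumours above 1 cm.
- Assumed, because the document gives nothing: the distribution of size, the odds ratio (OR) for choosing surgery per cm, and the strength of the size-outcome relation.

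**One case by hand.** Take size uniform on 0.5-2.0 cm (SD 0.433 cm) and an OR of 2 per cm. Large-sample simulation gives a crude size difference of 0.1281 cm and a within-band difference of 0.0458 cm. The share left is 0.0458/0.1281 = 0.36. With an outcome slope of 0.3 SD per SD of size, the remaining bias is 0.3 × 0.0458/0.433 = 0.032 SD.

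**Range** (2,000,000 simulated patients, slope 0.3 SD per SD of size, no true effect):

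| Size distribution (assumed) | OR per cm | Crude bias (SD) | After 1 cm split (SD) | Share left |
|---|---|---|---|---|
| Uniform 0.5-2.0 cm (67% above 1 cm) | 1.5 | 0.053 | 0.018 | 35% |
| Same | 3.2 | 0.144 | 0.054 | 37% |
| Same | 10 | 0.26 | 0.11 | 43% |
| Half 0.5-1 cm, half 1-2 cm | 1.5 | 0.054 | 0.015 | 28% |
| Same | 3.1 | 0.15 | 0.045 | 30% |
| Same | 9.8 | 0.28 | 0.097 | 34% |

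A weaker size-outcome relation scales the bias down in proportion. At 0.1 SD per SD, the OR 1.5 rows give about 0.005-0.006 SD. The rows with OR near 3.2 and 10 correspond to 1.65 and 2.72 per SD of size. They are strong: across 0.5-2.0 cm they imply 3.2^1.5 ≈ 5.7-fold and 10^1.5 ≈ 32-fold odds of surgery.

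**Continuous term.** With error-free diameter and a linear relation, the remaining bias is 0 by construction. With an assumed ultrasound error of 1.5 mm SD, it is about 0.006 SD (OR 1.5) to 0.035 SD (OR near 10). This is smaller than after the split in every row, but not zero.

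**Yardstick.** The unadjusted 95% half-width for a mean difference in SD units is 1.96 × √(1/330 + 1/120) = 1.96 × 0.1066 = 0.21 SD.

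**The case against.** The strongest case against the point has four parts.

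1. *The links are assumed.* The document has no data relating size to choice. The reasons that it reports are avoidance of surgery and thyroid hormone on one side and removal of the cancer on the other. It also has no data relating size to quality of life, anxiety, survivor concerns or regret. This stands: the bias is conditional, and its size is illustrative.

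2. *The split does most of the work.* A reader might infer that cutting at 1 cm discards the confounder. The arithmetic does not support that. In the table, the split removes 57-72% of the size-related bias.

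3. *The reach is limited.* A reader might infer that the main result is affected. The document does not support that either. It says "The primary analysis will separately estimate the cumulative incidence of ‘failure’ of disease management (along with 95% confidence intervals" by arm and names no covariates there, nor for the difference between arms. The adjustment sentence belongs to the secondary and questionnaire outcomes. The remaining bias is also smaller than the 0.21 SD half-width. That comparison only partly reassures, since bias does not shrink with more patients and moves the centre of the interval.

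4. *The cut is not arbitrary, and a full analysis plan may refine it.* One centimetre is the microcarcinoma limit, and the Introduction explains that most AS evidence lies at or below it. The covariate list is open, and the next sentence names tumour size without a cut. The limit is a good reason to display results by band, but no reason is given for using it as the adjustment term. An open list allows further covariates; it does not alter the form stated for size.

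**Conclusion.** The point holds as a minor matter of method, confined to the adjusted secondary and patient-reported comparisons. The plan states a coarser form of a covariate than its data allow, in a study where patients choose their management.

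If size is related to both choice and outcome within the bands, roughly 25-40% of the size confounding remains, or about 0.01-0.11 SD. The upper end needs very strong selection by size; with about half the tumours above 1 cm and an OR of 1.5 per cm it is nearer 0.015 SD. If size has no such within-band relation, the split leaves no size confounding. The document contains no contradiction or wrong figure on this point, and neither the primary estimates nor the sample size changes.

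**What to change.** In the adjusted models for secondary and patient-reported outcomes, replace the two-level size term with baseline ultrasound maximal diameter as a continuous covariate. A linear term is enough as a default. A restricted cubic spline with 3 knots can be specified where the number of patients or events allows, to cover a curved relation. Keep the split at 1 cm for descriptive tables and subgroup display, where it links to the microcarcinoma literature.

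The cost is a change of wording. The measurement is already collected, the linear term uses the same single degree of freedom as the split, and the spline uses one more. The report should say that, because of ultrasound measurement error, some size confounding may remain even with the continuous term.

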### Informed Consent, Ethics Review, and Data Safety and Monitoring

The original single-centre study in Toronto was approved by the University Health Network Research Ethics Board (ID 15-8942); expanded participant recruitment in Toronto (beyond the original sample size of 200 participants in 15-8942) and the addition of other Ontario sites is provincially approved by the Ontario Cancer Research Ethics Board (ID 1986). At the time of writing of this manuscript, the Ontario Research Ethics Board has approved the Toronto, Ottawa, and London, Ontario sites, with the Hamilton application awaiting completion by the site investigator. Respective research ethics board approval has also been obtained at the following sites: Halifax, Quebec City, and Vancouver. Otherwise, individual research ethics board applications are in progress for other planned participating sites (Hamilton, Calgary, and Montreal).

Aggregate data on the study recruitment rate in both arms, rates of surgery, AS, and AS cross-over, and thyroid cancer outcomes as well as serious adverse events (defined by death due to thyroid cancer or development of distant metastatic thyroid cancer) will be reported yearly to an independent Data and Safety Monitoring Committee (DSMC) made up of representatives who are independent of investigators. The DSMC will provide a yearly summary, outlining any concerns or suggestions, and providing approval for continuation of the study.

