### Study Follow-Up Assessments and Outcomes

As in the original study (9), AS routine follow-up includes clinical assessment (comprised of neck ultrasound at the participating institution, bloodwork (TSH, thyroglobulin, thyroglobulin antibody), and investigator clinical evaluation) every 6 months for two years, then yearly if there has been no evidence of disease progression. More frequent assessments or additional investigations may be performed if there is a clinical concern. Indefinite clinical follow-up at a participating study site is offered for patients as long as they are undergoing AS. The criteria for recommending surgery for disease progression (the same as in the original study) are defined as any of: 1) primary tumor growth > 3mm (in largest diameter, confirmed on two consecutive ultrasound exams); 2) PTC growth in a location that is concerning (i.e. encroaching the trachea or course of the recurrent laryngeal nerve or grossly invading extrathyroidal tissues); or 3) incident nodal metastatic disease, or 4) incident distant metastatic disease (**Table 2**) (9). Furthermore, as in the original Toronto study, patients under AS are free to choose to cross over to surgery in the absence of disease progression at any point in follow-up and may continue to be followed in the study (in a manner analogous to that of patients who choose immediate surgery) (9). In patients initially choosing surgery or crossing over from AS to surgery, the extent of surgery and any other treatments will be at the discretion of the treating surgeon or thyroid cancer specialists (who are not mandated to be at a participating study site), and is intended to reflect usual care. Typical post-surgical disease surveillance of patients treated for VL-PTC includes periodic clinical evaluations, neck ultrasounds, and bloodwork (TSH, thyroglobulin, thyroglobulin antibody), with additional investigations considered depending on the clinical circumstance. In the event that the clinical criteria for salvage surgery are met, it is expected that the treating or referring surgeon will perform thyroid surgery, but the patient may opt for a surgeon of her or his choice at any institution (usual care). Although highly unlikely, it is possible that a patient may decline surgery (e.g. due to development of new co-morbidity, or other reasons). Any occurrence of non-compliance with a recommendation for salvage surgery will be recorded, including the reason. However, based on our experience in Toronto, although sometimes patients may delay recommended surgery (e.g. due to life circumstances or COVID-19 pandemic related reasons), we have not had any patient completely refuse surgery and to date, ultimately all patients who were advised to have surgery by study investigators have done so. In the case of patients who initially decline surgery, close AS follow-up will continue, with imaging and clinical follow-up frequency per discretion of the study investigator (typically 3 to 6 months).

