Yearly follow-up questionnaires (up to 5 years) include: an update of thyroid cancer status and thyroid cancer treatments as well as the following questionnaires: i) quality of life (thyroid cancer/cancer-specific - EORTC QLQ-THY34 (12) with EORTC QLQ-THY34 (13) ii) anxiety (Generalized Anxiety Disorder Screener, GAD-7) (14), iii) survivors’ concerns (Assessment of Survivor Concerns, ASC [1])), and iv) decision regret, relating to the original decision to undergo AS or surgery [decision regret scale (15)]. The questionnaires used in this study to evaluate quality of life and psychosocial outcomes have all been previously used in cancer populations.

For sites in the province of Quebec using French language EORTC QLQ-THY-34 (12) and ASC (16) adapted to Quebec French are not available at the time of initiation of this protocol so they will be initially omitted, with the intention of incorporating them once available (after approval of research ethics board amendments in sites in the province of Quebec).

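### Thyroid-cancer death and distant metastasis go to the DSMC yearly and in aggregate, with no event-triggered report described, so an event already known to a site can wait up to 12 months

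*Protocol article*

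**What the plan says.** The section Informed Consent, Ethics Review, and Data Safety and Monitoring defines two serious adverse events and fixes when the committee receives them: "serious adverse events (defined by death due to thyroid cancer or development of distant metastatic thyroid cancer) will be reported yearly". They share one aggregate report with recruitment rates, rates of surgery, AS and cross-over, and thyroid cancer outcomes. The committee's response runs on the same interval: "The DSMC will provide a yearly summary, outlining any concerns or suggestions, and providing approval for continuation of the study".

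The Introduction says of these events: "No thyroid cancer-related deaths nor incident distant metastases have been observed in patients with small, low risk PTC under AS". It adds that most published AS work concerns tumours of 1 cm or smaller, and that about half of the enrolled Toronto patients had a larger tumour. Eligibility extends to tumours below 2 cm. Study Aim and Primary Outcomes makes the safety of AS relative to immediate surgery the primary research objective.

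Study Follow-Up Assessments and Outcomes gives several ways in which the study can learn of an event:

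- AS visits take place "every 6 months for two years, then yearly if there has been no evidence of disease progression", and "More frequent assessments or additional investigations may be performed if there is a clinical concern".
- Records: "Thyroid cancer-related medical records will be reviewed by study staff at least yearly, for up to 10 years".
- Patients: "Yearly follow-up questionnaires (up to 5 years) include: an update of thyroid cancer status and thyroid cancer treatments".

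Sites also enter data into a central electronic database, as the recruitment section says. The article does not say how soon after an event the entry is made.

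**The concern.** A yearly aggregate suits events that build up into a rate. These two do not: the article's own evidence puts the count under AS at zero, so one case is already the information, and nothing is gained by holding it for a yearly table. The zero is also least well supported where this study goes beyond the literature, in tumours above 1 cm.

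At stake is when the body that approves continuation learns of a case. Patients choose between AS and surgery after reading a written summary of the literature, and AS patients may cross over to surgery at any time. A case would bear on both decisions, and the committee is the independent body placed to judge whether it should change what patients are told. The stated timetable lets it learn of the case up to a year after a site does.

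**Working it through.** The article states no reporting delay, so there is no figure of the plan to reproduce. The delay follows from the stated intervals.

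**Inputs**

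- R, interval between DSMC reports: 12 months (monitoring section).
- D, longest interval until the study learns of the event (follow-up section):
  - 0 months if the event is known and recorded at once;
  - 6 months if it is found at a scheduled AS visit in the first two years;
  - 12 months if it is found only at a yearly AS visit or a yearly record review. The record review is stated as a minimum frequency, so 12 months is its longest gap.

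**Formulas**

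- Maximum delay = D + R.
- Mean delay = D/2 + R/2, if the event falls at a random time within each interval.
- Chance of a delay above 12 months = (D/2)/12 for D up to 12. Given a first wait d, the total exceeds 12 months when the second wait exceeds 12 − d, which has probability d/12. Averaging over d gives (D/2)/12. This also needs the two cycles to be independent.

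**Results**

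| How the study learns of the event | Maximum (months) | Mean (months) | Chance of more than 12 months |
|---|---|---|---|
| Known and recorded at once | 0 + 12 = 12 | 0 + 6 = 6 | 0 |
| 6-monthly AS visit, years 1–2 | 6 + 12 = 18 | 3 + 6 = 9 | 3/12 = 25% |
| Yearly-only ascertainment | 12 + 12 = 24 | 6 + 6 = 12 | 6/12 = 50% |

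A simulation with one million draws per row agreed: means 6.0, 9.0 and 12.0 months, and chances 0, 25% and 50%.

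**Reading the rows.** The first row needs only the stated reporting interval and the absence of a faster route; it carries the point. The second and third add a detection delay that the article bounds but does not fix. The third applies mainly to AS after year two, and to surgical or crossed-over patients, whose treating specialists need not be at a study site.

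**The case against.** The strongest objection is that this is a condensed article. Expedited notice of single cases, ad hoc meetings and reports to ethics boards often sit in a full protocol or a DSMC charter, and neither is shown. This stands to the extent that one cannot say the study has no faster route. It does not remove the point, because the article states an interval for these two events by name. If a faster route exists, the stated rule is incomplete and needs a cross-reference.

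A second objection is that patient care does not wait for the committee. This is right for the affected patient: "4) incident distant metastatic disease" is itself one of the criteria for recommending surgery. The central investigators are also available to advise sites throughout, and investigator meetings are yearly or more frequent. Nothing prevents the investigators from acting on a case before the yearly report, so it would be wrong to say that patients must go on choosing on contradicted information. But none of this tells the independent committee.

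Third, the study is observational with no assigned intervention. That lowers the urgency. It does not explain why a committee asked to approve continuation should receive these events only on a yearly schedule.

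Two stronger readings are tempting and are not supported. A reader might infer that the DSMC report is built on the yearly record review, so that a two-year wait is the ordinary case. The article does not link the two, the review is at least yearly, and visits, site data entry and questionnaires are other sources. If the review did feed the report, the cycles would be linked and the wait would be nearer one cycle; 24 months needs yearly-only ascertainment and the worst alignment of two unlinked cycles. A reader might also want to count the patients who choose AS during the delay. The article gives no recruitment period, so any such count would rest on an assumption.

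**Conclusion.** The point holds for the stated reporting interval. As written, an event already known to a site can take up to 12 months, about 6 on average, to reach the DSMC. That is a poor match for two events with no reported occurrence under AS, in a study whose primary objective is the safety of AS and whose tumours extend beyond the size range of most of the evidence.

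The figures of 18 and 24 months are upper bounds on the time from event to committee, not typical delays. The means and percentages assume events at random times and independent cycles. The conclusion also assumes that no other document provides a faster route. The study is not invalid and its estimates are untouched; this is an inexpensive improvement to its safety monitoring.

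**What to change.** In the monitoring section, keep the yearly aggregate report and add that each thyroid-cancer death or distant metastasis is also sent to the DSMC as an individual case promptly after the site becomes aware of it. The case should give the study arm, tumour size, time since enrolment and surgery status. The committee then decides whether an ad hoc review or an update of the patient information is needed. The documents give no basis for a particular number of days, or for an automatic review of recruitment after one event, so neither needs to be fixed here.

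If the full protocol or DSMC charter already contains such a route, a sentence referring to it is enough.

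The cost is one sentence and a short case form, with expected use close to zero. The downside is an occasional unscheduled contact with the committee. Treatment, eligibility, sample size and analysis do not change.
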